## Abstract

**Background:**

There is increasing interest in stem cell therapy as another treatment modality in stroke, particularly for patients who are unable to receive endovascular clot retrieval or thrombolysis therapies, or for whom standard treatment has failed. We have recently shown that human amniotic epithelial cells (hAECs) are effective in reducing infarct volume in different animal models of ischemic stroke, including in non-human primates. hAEC therapy attenuated infarct growth and/or promoted functional recovery, even when administered 1–3 days after the onset of stroke.

**Methods:**

We now propose an open label Phase 1 dose escalation trial to assess the safety of allogeneic hAECs in stroke patients with a view to providing an evidence platform for future Phase 2 efficacy trials. We propose a modified 3 + 3 dose escalation study design with additional components for measuring magnetic resonance signal of efficacy as well as the effect of hAECs on immunosuppression after stroke.

**Result:**

The trial will commence in 2018. The findings will be published in a peer-reviewed journal.

**Conclusion:**

The trial is registered with ANZCTR (ACTRN12618000076279p).

## Introduction

Prior to 2015, the standard clinical approach for reducing disability and death in ischemic stroke was Stroke Unit admission, antiplatelet therapy, and treatment with recombinant tissue plasminogen activator (TPA), within 4.5 h from onset in selected patients (1). However, the rate of vessel re-opening when there is a large obstructive clot is low (12%), even with TPA (2). Since 2015, there has been considerable optimism about the place of endovascular clot retrieval (ECR), for large clot removal, as a new and transformative therapy (1). However, even with this extended time window (up to 24 h), the number of eligible patients for ECR is less than 15% (1, 3). Further, a substantial proportion of those patients in the trial who received these treatments was left with moderate to severe disability or died (72% of patients who received TPA and 48% of those who received TPA and ECR) (2). In short, there remain enormous challenges in achieving the effective management of stroke across all patients. There is thus an urgent need to explore alternative therapeutic strategies that may be both suitable for more stroke patients and be more effective in improving outcome after stroke.

One such strategy is to move from the current time-based approach to an imaging tissue-based approach where treatment is based on the presence of salvageable ischemic tissue (3, 4). However, reperfusion therapies shift the peri-infarct zone toward the ischemic core but do not address the local and systemic immune response cascades that separate from the ischemic insult itself, promoting further tissue damage surrounding the infarct (5). The body’s intended effect of post-stroke immunosuppression appears to be the dampening of the “autoaggressive” Th1 immune response within the brain (6), but the unintended consequence is an increased risk of infection such as pneumonia (7), and this phenomenon is associated with high mortality and poor functional outcomes. These infiltrating inflammatory cells are located in the peri-infarct area, which has been referred to as the “inflammatory penumbra,” which denotes an area susceptible to further injury from the inflammatory cascade (5). Recognition of the need to manage the inflammatory response as part of stroke therapy has led to a call for future therapies that also focus on mitigating injurious events in the peri-infarct zone and not just on reperfusion therapy (5). In this regard, stem cell therapy has emerged as one potentially attractive option because of its ability to modulate inflammatory pathways at multiple sites appropriate to the changing pathophysiological state over time (8). By contrast, an example of a unimodal neuroprotectant drug target that would be unsuitable for modulating the inflammatory cascade is matrix metalloproteinase (MMP-9). In the early phase of stroke, MMP-9 damages the blood–brain barrier (BBB) (9) and contributes to vasogenic edema, whereas in later stages, it contributes to remodeling around the peri-infarct areas, and consequently targeting MMP-9 at this time can be harmful (5).

### Human Amnion Epithelial Cell as a Cell Therapy

The amniotic membrane is the inner layer of the fetal sac and consists of epithelium, basement membrane, and stroma. Amnion epithelial cells are therefore adult cells that express surface markers common to those of embryonic stem cells, primordial germ cells, and somatic stem cells including neural crest cells (10). Human amniotic epithelial cells (hAECs) express nonpolymorphic, nonclassical human leukocyte antigen (HLA) G (11) and have “low” immunogenicity (12) due to their role in protecting the fetus from immune rejection. There are various mechanisms by which hAECs might exert therapeutic effects following stroke. First, hAECs could secrete neurotrophic factors that promote the recovery of damaged cells in the penumbra. Such factors could also promote synaptogenesis to re-innervate lost connections. Second, hAECs could differentiate into a neuronal phenotype and replace damaged or dead cells. Third, hAECs could act as “biological minipumps” within the central nervous system, secreting necessary cytokines, growth factors, hormones, and/or neurotransmitters to restore cellular function. Fourth, hAECs could improve stroke outcome by dampening of the innate and adaptive immune systems (suppression of pro-inflammatory cytokines and secretion of factors that inhibit chemotactic activity of neutrophils and macrophages) that contributes to brain injury, which would include protection of neurons from immune cell-mediated apoptosis (10, 13). Lastly, systemically administered hAECs could attenuate the severity of post-stroke immunosuppression involving marked leukopenia and atrophy of secondary lymphoid tissues. Figure 1 provides a schematic of the potential effects of hAECs on post-stroke inflammation and immunosuppression.

**Figure 1 F1:**
[figure not shown]
Action of amnion stem cell on inflammatory cascade post ischemic stroke.

We have evaluated the utility of an intravenous route for hAEC therapy in a series of experiments involving different animal models of stroke (C57Bl6 mice and marmoset monkeys; both sexes) (14). These experiments showed that hAECs can reduce infarct volume and functional deficit when given acutely or as long as 3 days after stroke onset (14). hAECs were detected in the brain (infarct) and spleen of animals subjected to stroke, but not in sham-operated animals that received hAEC (14), indicating that hAEC migrate to tissues impacted by stroke. Key effects at the peri-infarct zone and infarct core occurred *via* reductions in (1) apoptosis, (2) inflammation (i.e., reduced expression of inflammasome protein, NLRP3 at 24 h and dampened entry of neutrophils, CD8^+^ T cells, B cells, and pro-inflammatory macrophages into the infarct by 72 h), and (3) post-stroke immunosuppression (14). Over 8 weeks, there was a decreased spread of gliosis into the adjacent border in hAEC-treated mice. Further, long-term functional recovery was still augmented in either young or aged mice of both sexes even if hAEC administration was delayed until 1 or 3 days post stroke (14).

## Method

### Overall Plan

We have designed an open label Phase 1 dose escalation trial of hAECs in patients with ischemic stroke with the primary aim of determining the maximal tolerated dose (MTD). Assessment of adverse events will be undertaken blinded to cell dose. Fifteen patients will be recruited for a dose escalation trial in 2018. The final follow-up for the 15th patient in the hAEC arm will be done 12 months after cell delivery. The trial will be submitted to the Monash Health Human Research Ethics Committee.

### Inclusion Criteria

Patients are eligible if (1) they have ischemic stroke in the territory of the large main artery (middle cerebral artery) (15), (2) present within 24 h of stroke onset and are not eligible for TPA or clot retrieval, (3) age is between 18 and 85 years old, (4) have National Institute of Health Stroke Scale/NIHSS (tool used in clinical trials for measuring stroke severity) between 6 and 15, and (5) patient or person responsible (on behalf of participant) must sign consent form after explanation of the trial.

### Exclusion Criteria

Patients are excluded if (1) eligible for TPA and/or ECR; (2) there is evidence of autoimmune disease, organ transplant, malignancy, splenectomized individuals, or have infection at the time of stroke; (3) neurodegenerative disease such as dementia or Parkinson’s disease; (4) pregnancy; (5) have contraindications for magnetic resonance (MR) imaging such as pacemaker; (6) patients with initial infarct [on diffusion weighted imaging (DWI)] volume of ≤5 or >100 mL will also be excluded (14, 16). This is a common strategy used in many studies to exclude infarcts with very small volume (such as lacunar infarct); very large infarcts are excluded as these patients have a high probability of developing malignant middle cerebral artery infarct and death; (7) patients with mild stroke (NIHSS <6) or very severe stroke (NIHSS >15); (8) blood sugar level of ≤3 or ≥20 mmol/L; and (9) significant lung disease requiring oxygen.

### Treatment Doses

Treatment doses are of stage-wise dose escalation: 2, 4, 8, 16, and 32 million cells/kg.

### Infusion Protocol

Patients will be given hAECs by intravenous infusion for 1 h, previously shown to be safe in preterm babies. A recent study with multipotent adult progenitor cells showed that 1,200 million cells were infused up for 1 h (17). The maximal dose used in neural stem cell trial was 20 million cells/kg given by direct intracerebral injection (18).

### Sample Size

This trial is designed as a balance between finding the MTD and finding the effective dose (19). The dose escalation and de-escalation stages are performed similar to the classic 3 + 3 scheme in a Phase 1 trial whereby the sample size is increased in small increments of 3. For a 5-dose escalation, the estimated sample size is 15. The Bayesian Optimal Interval Design (BOIN) (20) used here weighs the dose escalation by the lower boundary of the target toxicity rate (safety rate = 0.6 × target) and de-escalation by the upper boundary (toxicity rate = 1.4 × target). This method recommends setting the default target rate at 0.3 rather than a lower value because of the small sample size typical for Phase 1 trial (20). This default is higher than 90-day mortality of 15.7% for patients at the Monash Medical Centre with NIHSS between 6 and 15. The map of this approach is provided in Figure 2 and Table 1. The rows show that the decision for escalating or de-escalating the dose can be performed by counting the number of patients with the observed toxicity.

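### Fifteen patients is one cohort of three per dose: it covers five doses only under uninterrupted escalation, and the protocol does not say so

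*Protocol article*

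**What the plan says.** Treatment Doses lists five levels: "Treatment doses are of stage-wise dose escalation: 2, 4, 8, 16, and 32 million cells/kg". Sample Size describes a scheme "whereby the sample size is increased in small increments of 3" and concludes: "For a 5-dose escalation, the estimated sample size is 15". Overall Plan turns the estimate into a recruitment number, "Fifteen patients will be recruited for a dose escalation trial in 2018", and sets the end of follow-up by the fifteenth patient.

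The same Sample Size section makes the design adaptive in both directions: "The dose escalation and de-escalation stages are performed similar to the classic 3 + 3 scheme". It names BOIN with a target DLT rate of 0.3 and multipliers of 0.6 and 1.4 for the lower and upper rates, and refers the reader to Table 1 for decisions.

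Table 1 assigns patients 1–3 to the first dose, 4–6 to the second, and so on to 13–15 at the fifth. Its escalation, de-escalation and stopping limits rise with patient number. Statistical Analysis, by contrast, works from patients and toxicities counted separately at each dose.

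**The concern.** A figure of 15 for five doses in threes has no slack. The gap between the escalation and de-escalation rows of Table 1 creates a third decision, to stay and treat three more at the same dose. Any stay or de-escalation uses a cohort that was meant for a higher dose. The section presents 15 as the size of a five-dose escalation without this condition.

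The Results section intends the MTD to set the Phase 2 dose. If the trial ends at 15 with upper doses untreated, a reader who takes the sample-size statement at face value could assume that all five doses had been examined.

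**Working it through.** **Inputs.** Five doses (Treatment Doses). Cohorts of 3, target t = 0.30 and multipliers 0.6 and 1.4, so p1 = 0.18 and p2 = 0.42 (Sample Size). Recruitment of 15 (Overall Plan). Limits by patient number (Table 1). DLT equivalent to any SAE (Safety). 90-day mortality 15.7% (Sample Size). The rates 0.05 and 0.10, and a rate that is flat across doses, are assumptions.

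**Step 1: the plan's own figure.** 5 × 3 = 15. It reproduces, as one cohort per dose.

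**Step 2: the boundaries.**
- Escalation: ln[(1 − p1)/(1 − t)] / ln[t(1 − p1)/(p1(1 − t))] = ln(0.82/0.70) / ln(0.246/0.126) = 0.2365.
- De-escalation: ln[(1 − t)/(1 − p2)] / ln[p2(1 − t)/(t(1 − p2))] = ln(0.70/0.58) / ln(0.294/0.174) = 0.3585.

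Rounding 0.2365n down and 0.3585n up for n = 1 to 15 reproduces the first two limit rows of Table 1 exactly. The stopping row reproduces as the smallest count for which the posterior probability of a rate above 0.3 exceeds 0.95 (uniform prior, n of at least 3). The printed limits are therefore BOIN limits for n patients at the current dose, set against trial-wide patient numbers.

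**Step 3: per-dose counting.** At n = 3, 3 × 0.2365 = 0.71 rounds down to 0, and 3 × 0.3585 = 1.08 rounds up to 2. So 0/3 escalates, 1/3 stays and 2/3 or more de-escalates. Five cohorts visit five doses only if all four decisions are to escalate, which means no DLT in patients 1–12. Classic 3 + 3 gives the same condition. With a flat rate p, the probability is (1 − p)^12.

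**Step 4: Table 1 as printed.** Escalation is allowed with cumulative DLTs of at most 0, 1, 2 and 2 after patients 3, 6, 9 and 12. The first three patients must be DLT-free. One later DLT can fall on any of 9 patients. Two can fall in C(9,2) − C(3,2) = 36 − 3 = 33 ways, because patients 4–6 may have at most one. The probability is (1 − p)^12 + 9p(1 − p)^11 + 33p²(1 − p)^10. At p = 0.10 this is 0.2824 + 0.2824 + 0.1151 = 0.680.

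| Flat DLT rate | Per-dose counting | Table 1 as printed |
|---|---|---|
| 0.05 | 54.0% | 84.6% |
| 0.10 | 28.2% | 68.0% |
| 0.157 | 12.9% | 49.2% |

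**Step 5: how much is due to the cap.** Under classic 3 + 3 with no limit of 15, a dose is passed at 0/3, or at 1/3 followed by 0/3. The fifth dose is then reached with probability [(1 − p)^3 + 3p(1 − p)^5]^4, which is 90%, 67% and 41% at the three rates. The per-dose column above is well below these, although all three rates lie under the design's own lower rate of 0.18.

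**The case against.** The strongest objection is that Table 1, the decision map to which Sample Size refers, is indexed by trial-wide patient number. Read that way, two DLTs among the first 12 need not block the fifth dose. This stands against any unqualified statement that a single DLT puts the fifth dose out of reach. It does not remove the point: the printed reading also needs four escalations in a row and budgets no patient for a stay or de-escalation. Per-dose counting has the support of Statistical Analysis and of the exact match in Step 2.

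A reader might infer that most realised trials would miss the fifth dose. The documents do not support that in general. Under per-dose counting the probability falls below one half only when p exceeds 1 − 0.5^(1/12) = 0.056. As printed, most trials reach the fifth dose at 0.05 and 0.10, and about half do at 0.157.

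A reader might also infer that 15 cannot yield an MTD. It can: BOIN may stop at 15 and select among the doses tried, and stopping short because a lower dose is toxic is the design working as intended. Sample Size also says the figure is estimated. That defence is limited, because Overall Plan states fifteen as the number to be recruited.

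The 0.157 case is illustrative. It is mortality over 90 days, while the only DLT review interval given is 7 days, for the first cohort. On the other hand, DLT includes non-fatal SAEs. The true rate could be lower or higher.

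Two neighbouring points are not part of this one. Simulated operating characteristics may sit in the full protocol or SAP, so their absence from an article is no fault. The phrase "This trial is designed as a balance between finding the MTD and finding the effective dose" does not say that efficacy enters the escalation rule, and it rests on a cited source.

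**Conclusion.** The point holds in a limited form. Fifteen is the least number that can visit five doses, and Overall Plan also makes it the number to be recruited. It covers all five only on an uninterrupted climb, which the protocol does not state. At assumed flat DLT rates of 0.05, 0.10 and 0.157 the probability of that climb is 54%, 28% and 13% under per-dose counting, and about 85%, 68% and 49% under Table 1 as printed. The gap between the two sets is itself a contradiction to resolve, since Table 1 and Statistical Analysis count DLTs differently.

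The 5 × 3 result and the boundaries follow from the protocol's own inputs. The percentages depend on the assumed rates, on independent patients and on a rate that does not change with dose.

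**What to change.** Keep 15 and change the wording in three places.

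- Sample Size and Overall Plan: state that 15 is a fixed maximum and covers all five doses only if escalation is never interrupted. If per-dose counting applies, this means no DLT in the first 12 patients.
- Sample Size, Table 1 and Statistical Analysis: state whether DLTs are counted at the current dose or across the trial, and align Table 1 with that choice. Which rule governs is for the sponsor to settle. The condition in the first change must match it, or the new text will contradict the table.
- Statistical Analysis and Results: state that the MTD and safety conclusions apply only to doses actually treated.

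The cost is a revised table or table heading, a few sentences and a less favourable description of what 15 patients can cover. No extra patients are required.

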**Figure 2 F2:**
[figure not shown]
Schematics of dose escalation and de-escalation.

**Table 1 T1:** Schematics of escalation and de-escalation dose [dose-limiting toxicity (DLT)].

Human amniotic epithelial cell dose (million cells/kg)	2	2	2	4	4	4	8	8	8	16	16	16	32	32	32
Patient number	1	2	3	4	5	6	7	8	9	10	11	12	13	14	15
Escalate drug dose if number of patients with DLT is ≤	0	0	0	0	1	1	1	1	2	2	2	2	3	3	3
De-escalate drug dose if number of patients with DLT is ≥	1	1	2	2	2	3	3	3	4	4	4	5	5	6	6
Stop trial if number of patients with DLT is ≥	NA	NA	3	3	4	4	5	5	5	6	6	7	7	8	8

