### Statistical Analysis

Descriptive statistics will be used to describe patient demographics, safety, and SAE of hAECs. The dose–response curve for estimating the MTD is performed using the BOIN package (20). This method computes the probability of toxicity (>0.3) given data base on the list of the number of patients treated at each dose and the number of toxicity at each dose. The MTD is denoted by a marked rise in the probability of toxicity from baseline.

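### Table 1 sets single-dose BOIN limits against a running patient count over five doses, so 2 of 3 DLTs can trigger escalation at 8 and 16 million cells/kg

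*Protocol article*

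**What the plan says.** The Sample Size section adopts BOIN, in increments of three patients, "setting the default target rate at 0.3 rather than a lower value". The lower limit is set by "safety rate = 0.6 × target" and the upper by 1.4 times the target. It adds: "For a 5-dose escalation, the estimated sample size is 15". It then makes the rows of Table 1 operative: "the decision for escalating or de-escalating the dose can be performed by counting the number of patients with the observed toxicity".

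Table 1 has a dose row (2, 4, 8, 16 and 32 million cells/kg, three columns each), a patient number from 1 to 15, and three rows of limits:

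- escalate at or below 0,0,0,0,1,1,1,1,2,2,2,2,3,3,3;
- "De-escalate drug dose if number of patients with DLT is ≥" 1,1,2,2,2,3,3,3,4,4,4,5,5,6,6;
- "Stop trial if number of patients with DLT is ≥" NA,NA,3,3,4,4,5,5,5,6,6,7,7,8,8.

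The Statistical Analysis section estimates the MTD from "the number of patients treated at each dose and the number of toxicity at each dose". The Safety section equates a DLT with an SAE, including death.

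**The concern.** A BOIN limit is a limit on the DLT proportion at the dose now being given, so its index is the number of patients treated at that dose. Table 1 indexes it by everyone treated so far, at any dose. The limits therefore loosen as the dose rises, although each new dose starts with three patients and no information of its own. If the table is followed as printed, the dose is doubled after two of three patients have had an SAE, and the primary aim, the MTD, rests on a rule that can hardly step down at the doses where toxicity is most likely.

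**Working it through.** **Inputs (Sample Size).** Target 0.30; safety rate 0.6 × 0.30 = 0.18; toxicity rate 1.4 × 0.30 = 0.42; cohorts of 3; five doses; 15 patients.

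**Reproducing the table.**

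- Escalation boundary: ln[(1−0.18)/(1−0.30)] / ln[0.30(1−0.18)/(0.18(1−0.30))] = 0.2365.
- De-escalation boundary: ln[(1−0.30)/(1−0.42)] / ln[0.42(1−0.30)/(0.30(1−0.42))] = 0.3585.
- Third row: the smallest y with Pr(rate > 0.3) > 0.95 under Beta(1+y, 1+n−y), for n ≥ 3. The uniform prior, the 0.95 cut-off and n ≥ 3 are assumptions and affect this row only.

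Rounding 0.2365n down and 0.3585n up, with the third-row rule, reproduces all 45 cells for n = 1 to 15, where n is the number of patients at one dose. The numbers are right; the index is wrong.

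**Reading the table at the end of each cohort.** If earlier cohorts were clean, the cumulative count and the count at the current dose are the same number, so these results hold on either reading.

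| Dose (patient) | 0/3 | 1/3 | 2/3 | 3/3 |
|---|---|---|---|---|
| 2 (3), the n = 3 column | escalate | stay | de-escalate | stop row met |
| 4 (6) | escalate | escalate | stay | de-escalate |
| 8 (9) | escalate | escalate | escalate | stay |
| 16 (12) | escalate | escalate | escalate | stay |
| 32 (15) | escalate | escalate | escalate | escalate |

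In the last row, *escalate* means that the entry (≤ 3) is met; there is no higher dose. De-escalation at 8, 16 and 32 needs at least 4, 5 and 6 DLTs, and stopping needs at least 5, 7 and 8. Three patients cannot supply these.

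**If earlier cohorts were not clean, the readings differ.**

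- Cumulative count: de-escalation is possible at 8 (DLTs 0, 1, 3 give 4 at patient 9) and at 16 (0, 1, 1, 3 give 5 at patient 12). It is impossible at 32: reaching 32 needs at most 2 DLTs by patient 12, so at most 2 + 3 = 5 by patient 15, below the entry of 6.
- Current-dose count: the first three patients cannot trigger de-escalation at the end of the 8, 16 or 32 cohort, or stopping at any dose from 4 upward.

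**Probabilities at 16 million cells/kg after nine clean patients.** The printed row escalates unless all three have a DLT, with probability 1 − p³. The n = 3 column escalates on 0/3, with probability (1 − p)³, and steps down or meets the third row on 2 or more, with probability 3p²(1 − p) + p³.

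| True DLT rate p | Printed: escalate | Printed: de-escalate | n = 3: escalate | n = 3: de-escalate or eliminate |
|---|---|---|---|---|
| 0.45 | 0.91 | 0 | 0.17 | 0.43 |
| 0.60 | 0.78 | 0 | 0.06 | 0.65 |
| 0.70 | 0.66 | 0 | 0.03 | 0.78 |

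**Exposure.** I simulated 60,000 trials per scenario, with cohorts of 3 and 15 patients; a *stay* adds a cohort at the same dose. The table gives mean patients treated at doses with a true DLT rate above 0.42. The rates are assumed.

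| True rates, lowest to highest dose | Printed, cumulative count | Printed, current-dose count | Per-dose rule |
|---|---|---|---|
| 0.05/0.10/0.16/0.50/0.60 | 5.2 | 5.4 | 2.5 |
| 0.02/0.05/0.10/0.20/0.45 | 2.6 | 2.8 | 0.9 |
| 0.45/0.50/0.55/0.60/0.65 | 11.3 | 11.4 | 11.4 |

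Where no dose exceeds 0.42, the measure is zero for every rule.

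**The case against.** The intended conduct may be sounder than the table. The article names BOIN, likens its steps to a 3 + 3 scheme and estimates the MTD from per-dose counts. The table is captioned as a schematic, Figure 2 cannot be seen, and a team running the software on per-dose counts would decide correctly. This limits what can be said about actual harm. It does not repair the printed counts, which the Sample Size section makes the decision rule. The software is cited for estimating the MTD, not for escalation. The DSMB review is described only for the step from cohort 1 to cohort 2, which is the one cohort whose columns are right.

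Four narrower points stand in part:

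- The statements that de-escalation or stopping cannot occur apply to the three patients that Table 1 allots to each dose. If a *stay* adds patients, later columns can be met: on a current-dose count, 3/3 at 8 followed by two more DLTs by patient 12 gives 5, the de-escalation entry.
- The per-dose wording in Statistical Analysis describes the final estimate. It supports the per-dose reading but does not itself state the escalation rule.
- Stopping the whole trial where BOIN would drop a dose is a defensible, more cautious choice, so the third row needs clarifying rather than condemning.
- The excess exposure arises when low doses are safe and a high dose is toxic. With every dose toxic (third scenario) there is none.

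**Conclusion.** The concern holds and should be corrected before the table is used. Correct single-dose limits have been printed against the wrong index, and only the 2 million cells/kg columns are right. After clean earlier cohorts, 2 of 3 DLTs escalates at 8 and 16 million cells/kg where the stated design de-escalates, and 3 of 3 at 8, 16 or 32 neither de-escalates nor stops. This follows from the printed entries and needs no assumed toxicity rate. The size does depend on the true rates: in the two scenarios with a toxic high dose, about two to three times as many patients are treated at doses above the 0.42 toxicity rate. The prior and cut-off assumed for the third row do not bear on the escalation or de-escalation finding.

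**What to change.** - Head the columns of Table 1 as the number of patients treated at the current dose, delete the dose row, and state that DLTs are counted at that dose. For three patients: 0 escalate, 1 stay, 2 or more de-escalate.
- Relabel the third row as eliminating that dose and all higher ones, with the trial stopped only if the lowest dose is eliminated; or have the sponsor and DSMB state the stopping rule they want.
- Say that 15 patients do not guarantee that all five doses are tested.

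The drafting cost is one table and a sentence or two in an amendment. The real cost is reach. With 15 patients in cohorts of three, the top dose is reached only if the first four cohorts, 12 patients, have no DLT. That has probability (1 − p)¹²: 0.95¹² = 0.54 at a flat 5% DLT rate, and 0.843¹² = 0.13 at a flat 15.7%, the 90-day mortality quoted in Sample Size. The sponsor must accept this or raise the sample size.

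### Table 1's trial-stop row holds boundary figures for a single DLT rate, but its label and patient-number columns apply them to the whole trial without fixing the counting unit or scope

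*Protocol article*

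**What the plan says.** The Sample Size section names the design ("The Bayesian Optimal Interval Design (BOIN) (20) used here"), the target ("This method recommends setting the default target rate at 0.3 rather than a lower value"), and the two rates that set its boundaries ("safety rate = 0.6 × target" and "toxicity rate = 1.4 × target"). Its account of conduct is that "The dose escalation and de-escalation stages are performed similar to the classic 3 + 3 scheme in a Phase 1 trial", where "the sample size is increased in small increments of 3". It says that escalation and de-escalation follow from counting patients with toxicity. It does not say whether that count is per dose or over the trial, and it does not mention a trial stop.

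Table 1 gives three rows of limits, for escalating, for de-escalating, and "Stop trial if number of patients with DLT is ≥". The columns number patients 1 to 15 consecutively, three to each dose from 2 to 32 million cells/kg. The stop row reads NA, NA, 3, 3, 4, 4, 5, 5, 5, 6, 6, 7, 7, 8, 8, with no restriction to any dose.

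The Statistical Analysis section estimates the MTD from the "number of patients treated at each dose and the number of toxicity at each dose", that is, from per-dose counts.

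**The concern.** A count that is too high at one dose is evidence about that dose. It is evidence that no studied dose is acceptable only when the dose is the lowest. The stop row's figures are of the first kind and its label is of the second. Its columns, which run on across doses, suggest a third use, with all patients pooled.

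The primary aim is the MTD, which is meant to inform the Phase 2 dose. If a high count at a higher dose ends the trial, patients not yet enrolled cannot add safety data at the dose below, which is then the likely recommendation. If the counts are pooled instead, the same figures respond too weakly to toxicity at the current dose. Either way, the people running the trial would have to guess which was meant.

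**Working it through.** **Inputs from the protocol.** Target 0.30; lower rate 0.6 × 0.30 = 0.18; upper rate 1.4 × 0.30 = 0.42; cohorts of 3; 15 patients; Table 1.

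**Inputs assumed.** Uniform Beta(1,1) prior, cutoff 0.95, and no stopping before n = 3. The protocol prints none of these.

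**Step 1: reproduce the escalate and de-escalate rows.**

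- Lower boundary: ln(0.82/0.70) / ln[(0.30 × 0.82)/(0.18 × 0.70)] = 0.2365.
- Upper boundary: ln(0.70/0.58) / ln[(0.42 × 0.70)/(0.30 × 0.58)] = 0.3585.
- Rounding n × 0.2365 down and n × 0.3585 up gives all 15 entries of each row.

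**Step 2: reproduce the stop row.** Take the smallest y with 1 − BetaCDF(0.30; 1 + y, 1 + n − y) > 0.95. Examples:

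- n = 3: y = 2 gives 0.916; y = 3 gives 1 − 0.3⁴ = 0.992, so the limit is 3.
- n = 6: y = 3 gives 0.874; y = 4 gives 0.971, so the limit is 4.
- n = 9: y = 4 gives 0.850; y = 5 gives 0.953, so the limit is 5.

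For n = 3 to 15 the result is 3, 3, 4, 4, 5, 5, 5, 6, 6, 7, 7, 8, 8, identical to the table. Only cutoffs from about 0.950 to 0.953 reproduce it; 0.90, 0.96 and 0.975 each miss at least one entry. The calculation contains one rate and one n, so it describes patients who share one dose.

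**Step 3: per-dose counting.** The first cohort at a dose uses the n = 3 column, where de-escalation applies at 2 or more and the stop at 3 or more. Three of 3 DLTs meets both. With straight escalation and no earlier DLT:

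| 3 of 3 DLTs at (million cells/kg) | Trial ends at | Unspent of 15 | Patients at the dose below |
|---|---|---|---|
| 4 | 6 | 9 | 3 |
| 8 | 9 | 6 | 3 |
| 16 | 12 | 3 | 3 |
| 32 | 15 | 0 | 3 |

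With 0 of 3 DLTs, the one-sided 95% upper limit for the DLT rate is 1 − 0.05^(1/3) = 63%. For scale only, 0 of 12 (these 3 plus the 9 unspent in the first line) would give 1 − 0.05^(1/12) = 22%.

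**Step 4: how often, under per-dose counting.** All paths in cohorts of 3, to a maximum of 15 patients, were enumerated exactly for assumed DLT rates at the five doses.

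| Assumed DLT rates | Stop row met above the lowest dose | Of all trials, cut short there with patients unspent |
|---|---|---|
| 0.16/0.60/0.80/0.90/0.90 | 56.9% | 43.9% |
| 0.16/0.16/0.55/0.70/0.80 | 27.1% | 13.6% |
| 0.10/0.20/0.30/0.50/0.70 | 11.1% | 5.5% |
| 0.16/0.20/0.30/0.45/0.60 | 8.5% | 4.3% |
| 0.10/0.15/0.20/0.30/0.50 | 4.7% | 2.0% |
| flat 0.157 | 1.7% | 1.1% |

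The flat 0.157 borrows the 90-day mortality quoted in Sample Size. When the first cohort at a higher dose has 3 of 3 DLTs, the dose below has exactly three patients in 64% to 84% of cases over seven assumed curves, and otherwise six or nine. In a simulation of the two steepest curves (40,000 runs, isotonic MTD selection), applying the row to the trial or only to the dose moved the selected dose by no more than 1 percentage point.

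**Step 5: cumulative counting.** Take 3 of 3 DLTs at the current dose after none at lower doses, and read Table 1 at the running patient number:

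| Patients so far | Escalate if ≤ | De-escalate if ≥ | Stop if ≥ | Result for 3 DLTs |
|---|---|---|---|---|
| 6 | 1 | 3 | 4 | de-escalate |
| 9 | 2 | 4 | 5 | neither escalate nor de-escalate |
| 12 | 2 | 5 | 7 | neither escalate nor de-escalate |
| 15 | 3 | 6 | 8 | escalate limit met |

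The stop row is never met. From patient 9 on, the de-escalate row is not met either, although every patient at the current dose had a DLT.

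**The case against.** The strongest objection is that the premature stop depends on a reading that Table 1 does not print. Its consecutive patient numbers look cumulative, and then 3 DLTs after none never stops the trial. The per-dose counts in Statistical Analysis concern the final MTD estimate, not the escalation decisions. This stands: a reader might infer that the protocol as written ends the trial after 3 of 3 DLTs at any higher dose, and the document does not establish that. It does not rescue the row, because single-rate figures applied to pooled doses produce the dilution in Step 5. Nor does pooling make them a boundary derived for the whole trial.

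A second objection is that the rows are nested, so that the more severe action naturally governs, and that halting after 3 of 3 events equivalent to SAEs is defensible caution. That may be the intention, and nothing here argues against it. But Table 1 does not say so, and the figures were not built for it. The silence of Sample Size on a trial stop is weak evidence, because Figure 2 is not shown.

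A third objection concerns size. A reader might take 27% and 57% as the share of trials ended early. Those totals include trials that meet the row at patient 15, when nothing is left to lose; the shares cut short are 13.6% and 43.9%. Both curves also assume a jump from 16% to 55–60% in one dose step. Milder curves give 1.1% to 5.5%. Three patients per dose is in any case what 15 patients over five doses gives without any stop, and the MTD estimate draws on all doses, not only on those three. All of this stands and limits the point to one of precision.

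**Conclusion.** The point holds as a mismatch between the stop row's figures, its label and its columns. The figures are a single-rate boundary; this rests on a match in every entry from n = 3 to 15 and on an inferred prior and cutoff. On per-dose counts the row can end the trial above the lowest dose with patients unspent and often only three at the dose below. How often depends on the assumed curve: 1.1% to 5.5% for mild or moderate ones, and 13.6% and 43.9% for the two steep ones. On cumulative counts the row is diluted by lower-dose patients. The document does not settle which count applies.

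A wrong choice of dose is not shown, since selection hardly changed in simulation. In straight escalation nothing is lost at 32 million cells/kg. The mismatch is worth correcting before the first cohort because the correction is cheap.

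**What to change.** Reconcile the stop row's label, its figures, the patient-number columns, the de-escalate row, and the Sample Size and Statistical Analysis text, so that they agree on three things:

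- whether DLTs are counted per dose or over the trial;
- whether the printed figures apply to a dose or to the trial;
- which row governs when the de-escalate and stop rows are both met.

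If a trial-level boundary is intended, its figures should be derived for that purpose. The prior and cutoff behind the row could be stated at the same time. Which stopping rule to adopt is for the sponsor and the DSMB, and the DSMB's own power to stop is unaffected.

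The cost is one table row and one sentence, with no patients beyond the planned 15. The small downside is that, depending on the sponsor's choice, the trial may run on to its planned 15 patients.
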